## INVESTIGATIONAL PRODUCTS; DOSAGE, AND METHOD OF ADMINISTRATION

### INVESTIGATIONAL PRODUCTS:

Atorvastatin is administered orally once daily in doses of 40 or 80 mg.

### REFERENCE PRODUCTS:

Placebo orally once daily. Placebo is justified as long as the patient receives complete conventional antichagasic therapy, and therefore, management of his Chagas disease is assured.

**Antichagasic therapy (nifurtimox or benznidazole) will be administered to all study subjects, regardless of the study group to which they are assigned.**

### Efficacy analysis:

**Hypothesis:** Atorvastatin, in combination with conventional antichagasic therapy of nifurtimox or benznidazole, improves cardiac function in subjects with asymptomatic chronic-phase Chagas disease compared with placebo.

For analysis of the **primary outcome**, a one-sided Fisher's exact test of the proportion of patients with a significant decrease in biomarker levels in the ITT (primary analysis), and per protocol (secondary analysis) populations will be used. ANOVA test will be performed to analyze differences in variances between the different markers.

An exact test will be performed for all secondary comparisons of proportions between ATO versus placebo, including parasitological response to treatment. Latent class and multivariate analyses will assess parasitological response, biomarker changes, and ATO dose association.

If there are no significant differences between ATO treatments, these data will be collapsed into a single comparison group to obtain greater precision in the treatment effect estimate, given that this is a proof-of-concept study for statins as a class. In this case, no adjustment for multiple comparisons will be made.

**Safety Analysis:** Clinical assessments, electrocardiograms, and laboratory tests will be used to monitor the safety and tolerability of the drugs under study throughout the observation period of the subjects.

The proportion of patients presenting at least one AE will be described. The incidence rate and 95% confidence interval per study group will be presented. Otherwise, only descriptive statistics will be presented. Laboratory safety parameters (hematology and biochemistry) will also be described individually for each study group, showing the proportion of patients by degree of elevation relative to ULN and to baseline values and changes in blood levels over time.

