Although our preclinical studies were performed with simvastatin, we propose atorvastatin (ATO) as an experimental statin. As simvastatin is associated with ezetimibe, it will not be considered in this study. ATO's therapeutic and safety profiles are well known, as well as its mechanism of action and pharmacological actions, including its anti-inflammatory properties, which are shared by the other members of the statin class. Due to the low incidence of severe AEs and its efficacy, ATO is one of the most widely used statins. 20-80 mg/day of ATO are used to lower the so-called LDL cholesterol, implicated in the pathogenesis of the atherosclerotic cardiovascular disease. However, a clinical phase II proof-of-concept study is imperative because i) it is a way to translate the results obtained in the animal model, and ii) a minimum effective dose and safety need to be evaluated in the context of the patient undergoing treatment of chronic CD and, most importantly, iii) because statins are not currently approved for the treatment of CD.

Considering i) the high burden of disease; ii) the role of the endothelium and inflammation in the initiation and propagation of vascular wall injury in CD; iii) that current therapy for CD in the chronic phase is unsuccessful and increases the risk of systemic toxicity, AEs, and poor compliance; iv) that improving the efficacy of current antichagasic drugs by modifying host responses would make current treatment more effective; v) that preclinical evidence suggests that statins may have a role in preventing cardiac damage in CD; vi) that statins are safe and with a well-known pharmacological profile; then, a combination of trypanocidal drugs with those that induce resolution of the inflammatory process resulting from parasite persistence could be an effective therapeutic strategy to prevent the chronic consequences of CD. Consequently, it is proposed that the following hypothesis:

**In patients with chronic Chagas disease, statins improve the efficacy of antiparasitic treatment by decreasing inflammation and improving endothelial and cardiac function**

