### **12.Data analysis and statistical methods:**

#### **12.1. Sample size:**

A sample size of 75 patients per group is sufficient to achieve a power of 90% at an overall significance level of 5% (2-sided), assuming that the proportion of patients who improve electrocardiographic and echocardiographic parameters, as well as the levels of the cardiac function markers BNP and cTnT in the EOT in the experimental treatment group is 0.40. The proportion in the placebo group is 0.20, with an odds ratio of 2.5. Considering an estimated dropout rate of 25%, 100 patients per group (300 patients in total) would be recruited (Fleiss et al., 2003). The study will be sufficiently powered to provide evidence of the superior efficacy of either statin dose plus antichagasic therapy relative to antichagasic treatment alone.

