### **12.4. Efficacy analysis:**

For analysis of the primary outcome, a one-sided Fisher's exact test of the proportion of patients with a significant decrease in biomarker levels in the ITT (primary analysis) and per protocol (secondary analysis) populations will be used. ANOVA test will be performed to analyze differences in variances between the different markers. An exact test will be performed for all secondary comparisons of proportions between ATO versus placebo, including parasitological response to treatment. Latent class and multivariate analyses will assess the association between parasitological response, biomarker changes, and ATO doses.

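### The Summary lets a non-significant 40 mg versus 80 mg test decide whether the doses are pooled against placebo, so claims about either dose are not error-controlled and the contrast differs from the one section 12.1 promises

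*Protocol*

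**What the plan says.** Three places in the protocol bear on the contrast with placebo.

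- **Summary (section 6), Efficacy analysis.** After the sentences on the primary test, the secondary comparisons and the latent class analysis, it adds: "If there are no significant differences between ATO treatments, these data will be collapsed into a single comparison group". The stated gain is precision, and the stated reason is that this is a proof-of-concept study of the statin class. It continues: "In this case, no adjustment for multiple comparisons will be made". No test, level or endpoint is given for the dose comparison, and no adjustment is named for the case where the doses stay separate.
- **Section 12.1.** The trial is sized "at an overall significance level of 5% (2-sided"), and the paragraph ends: "The study will be sufficiently powered to provide evidence of the superior efficacy of either statin dose plus antichagasic therapy" over antichagasic treatment alone.
- **Section 12.4.** The main efficacy section names "a one-sided Fisher's exact test of the proportion of patients with a significant decrease in biomarker levels" for the primary outcome, gives no significance level, and says "An exact test will be performed for all secondary comparisons of proportions between ATO versus placebo". The pooling rule does not appear.

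**The concern.** A non-significant difference between two arms of about 75 patients is weak evidence that the doses act alike. Used as a gate, it makes the outcome data choose between two questions: does each dose beat placebo, or does atorvastatin overall beat placebo? If the doses differ and are still pooled, the estimate and its interval describe neither dose. A positive pooled result then credits a dose that may do nothing, and a negative one can hide a dose that works.

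Section 12.1 promises a conclusion about either dose, which a pooled test cannot give. Two analysts, one following the Summary and one following 12.4, could also report different comparisons from the same data.

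**Working it through.** **Inputs.** From 12.1: 75 evaluable per arm, placebo 0.20, experimental 0.40, 5% two-sided, 90% power, 25% dropout. From 12.4: one-sided Fisher test, level not stated, so both 5% and 2.5% are shown. Assumptions: the gate is a two-sided Fisher test at 5% on the same binary endpoint; there is no adjustment when the doses stay separate; the rates 0.20 (inert) and 0.30 (partly active) for the second dose are illustrative.

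**1. The plan's own figure.** n per group = [1.96·√(2·0.30·0.70) + 1.2816·√(0.40·0.60 + 0.20·0.80)]² / 0.20² = 108.2, so 109, not 75. At 75 per group the two-sided power is 76.7%. The dropout step, 75/0.75 = 100, is right. The 90% is therefore not reproduced. That is a separate matter, but the power statement has to be rewritten here anyway.

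**2. The rule as computed.** Let x₀, x₄₀, x₈₀ be the responders in each arm. If Fisher(x₄₀, x₈₀) gives p > 0.05, test (x₄₀ + x₈₀)/150 against x₀/75; otherwise test each dose against placebo. Probabilities are summed exactly over the three binomials.

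**3. Neither dose works (all 0.20).** The chance of any false claim is 4.0% at one-sided 5% and 2.0% at one-sided 2.5%. Over common rates from 0.05 to 0.95 it is at most 4.9% and 2.5%. With equal arms the 40–80 mg contrast and the pooled-placebo contrast are uncorrelated, so the act of pooling does not itself inflate this error.

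**4. One dose inert (0.20), the other at 0.40.**

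| | One-sided 5% | One-sided 2.5% |
|---|---|---|
| Trials pooled | 28.6% | 28.6% |
| Inert dose credited under the rule | 12.5% | 8.4% |
| Inert dose credited if tested directly | 3.3% | 1.5% |
| Any atorvastatin claim under the rule | 74.7% | 65.5% |
| Active dose tested directly | 80.9% | 71.4% |

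Of the 12.5%, 11.6 points come through pooling. Among pooled trials the estimated difference from placebo averages 0.096, against true values of 0 and 0.20, and the 95% interval covers each in about 60%. With all 100 randomised patients per arm, 15.6% are pooled and the inert dose is credited in 9.4% (one-sided 5%). The worst case is 14.5% to 14.6%, with the active dose at about 0.33 to 0.35.

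**5. Doses at 0.30 and 0.40.** 80% of trials are pooled. The pooled estimate then averages 0.149 against true effects of 0.10 and 0.20, and the interval covers the lower-dose effect in 86% and the higher-dose effect in 88%.

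**6. Power of pre-fixed alternatives** (normal approximation, two-sided 5%, 75 per arm).

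- *Each dose, Dunnett critical value 2.213:* Φ[(0.20 − 2.213·0.0748)/0.0730] = 68% (about 69% by simulation); about 84% for at least one dose if both are at 0.40.
- *Pooled 150 versus 75, both doses at 0.40:* Φ[(0.20 − 1.96·0.0667)/0.0611] = 87%. If one dose is inert it is about 35%.
- *Any-effect power, the rule versus the two-dose procedure:* 0.88 versus 0.84 (both doses 0.40), 0.72 versus 0.71 (0.30/0.40), 0.72 versus 0.69 (0.20/0.40).

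**The case against.** The strongest defence is that the Summary's hypothesis concerns atorvastatin against placebo and names no dose. For that question, a pooled rejection driven by one active dose is not a false positive. The rule is also written down in advance, so the data select a branch but nothing is changed post hoc. This stands, and it is why a pooled contrast fixed in advance is an acceptable cure. It does not rescue the gate, because 12.1 still promises a conclusion about either dose.

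A reader might infer several stronger points that the protocol does not support:

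- *The overall 5% is broken.* Not when neither dose works and the named Fisher test is used. About 6% arises only if ordinary z-tests replace it at one-sided 5%.
- *The gate mostly pools doses that differ.* True at 0.30 and 0.40, but at 0.20 and 0.40 about 71% of trials are not pooled.
- *Three sections fix three different primary contrasts.* The Summary has a rule and 12.1 has a promise, but 12.4 is silent.
- *The rule defeats a dose-finding aim.* The remark that "a minimum effective dose and safety need to be evaluated" belongs to the rationale in 7.2. The goals in section 8 contain no such aim, and analyses of dose association remain planned.
- *The rule expressly governs the primary outcome.* It follows the sentences on secondary analyses and names no endpoint. Applying it to the primary outcome is the natural reading, not an explicit one.

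**Conclusion.** The point holds for dose-specific claims and for estimation. The inert dose is credited nearly four times as often as under a direct one-sided 5% test (12.5% against 3.3%), and the chance of finding the active dose drops by about 6 points. When the doses differ moderately, four trials in five report an estimate that belongs to neither. These sizes rest on the assumed gate, on no adjustment in the unpooled branch, and on the 12.1 rates with 75 per arm; with 100 per arm the pattern is the same and the 12.5% becomes 9.4%. The mismatch between the Summary, 12.1 and 12.4 needs no assumption.

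**What to change.** Delete the condition about no significant differences between doses. State one primary contrast, in the same words in the Summary, 12.1 and 12.4, and say that it applies to the primary outcome:

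- **(a)** 40 mg versus placebo and 80 mg versus placebo under Holm or Dunnett at the overall 5%, with pooled atorvastatin versus placebo always reported as secondary. This matches the either-dose promise.
- **(b)** Pooled atorvastatin versus placebo as the single primary contrast, with each dose reported separately as secondary and the either-dose sentence in 12.1 withdrawn.

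Under both, report the 40–80 mg difference with its confidence interval, but not as a gate. State the significance level of the one-sided test and restate the power in 12.1.

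**Cost.** This changes wording only, with no new procedures or patients, provided the lower power is accepted. At 75 evaluable per arm, (a) gives about 69% per dose and 84% for at least one dose if both are at 0.40, and (b) about 87%, against the stated 90%. Option (a) gives up at most about 4 points of any-effect power relative to the present rule; option (b) loses much more if only one dose works. Restoring 90% would need, for (a) with Bonferroni, 129 evaluable per group (129/0.75 = 172 recruited, 516 in total), and for (b) 82 evaluable on placebo and 164 on atorvastatin.

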### Experimental Design Diagram

[figure not shown]

### Study Flowchart

| Phase                     | Pre-Randomization |          | Post-Randomization |    |     |                  |                  |     |
|---------------------------|-------------------|----------|--------------------|----|-----|------------------|------------------|-----|
| Period                    | Screening         | baseline | treatment          |    |     |                  | Follow-up        |     |
| Visit                     | 1                 | 2        | 3                  | 4  | 5   | 6                | 7                | 8   |
| Day(s)                    | -14 a -1          | 0        | 30                 | 60 | 120 | 180              | 240              | 360 |
| Procedure          |                   |          |                    |    |     |                  |                  |     |
| Informed Consent          | x                 |          |                    |    |     |                  |                  |     |
| Randomization             |                   | x        |                    |    |     |                  |                  |     |
| Clinical Record           | x                 |          |                    |    |     |                  |                  |     |
| Previous/concurrent drugs | ←-----→           |          |                    |    |     |                  |                  |     |
| Inclusion/Exclusion       | x                 | x        |                    |    |     |                  |                  |     |
| Vital Signs               | x                 | x        | x                  | x  | x   | x                | x                | x   |
| Complete physical exam    | x                 |          |                    |    | x   |                  |                  | x   |
| Chest X-ray               | x                 |          |                    |    | x   |                  |                  | x   |
| ECG                       | x                 |          |                    | x  | x   | (x) e | (x) e | x   |
| 2D Echocardiogram         | x                 |          |                    |    |     |                  |                  | x   |
| Pregnancy test            | x                 |          |                    |    |     | x                | x                |     |

|                                           |   |   |         |   |                |   |   |   |
|-------------------------------------------|---|---|---------|---|----------------|---|---|---|
| Serology                                  | x |   |         |   |                |   |   | x |
| Laboratory a                   | x | x | x       | x | x              | x | x | x |
| Quantitative PCR                          | x |   |         |   | x d |   |   | x |
| Biomarkers b                   |   | x |         | x | x              |   |   | x |
| Focused Physical Examination c | x | x | x       | x | x              | x | x | x |
| Adverse Events                            |   |   | ←-----→ |   |                |   |   |   |
| Drug Accounting                           |   | x | x       | x | x              |   |   |   |

aLaboratory parameters will include: hemoglobin, total white blood cell count, differential white blood cell count, and platelet count. Laboratory biochemical parameters will include: CK, ALT, AST, GGT, alkaline phosphatase, total and direct bilirubin, a lipid profile: total cholesterol, c-HDL, and c-LDL, triglycerides, fasting blood glucose, and creatinine;

bBiomarkers: BNP, cTnT, IFN- $\gamma$ , IL-1 $\beta$ , IL-4, IL-17A, e IL-10, sICAM-1, sVCAM-1, sE-selectin;

cPhysical examination focused only on the evaluation of adverse events.;

dPCR testing at these time points will be done with a single 10 ml sample;

eECGs will be performed at these visits only in case of previously identified abnormalities

## **7. Rationale and background:**

We postulate that statins, such as atorvastatin, due to their anti-inflammatory effect, improve vascular and cardiac inflammation in patients with asymptomatic chronic Chagas disease, contributing to the recovery of endothelial and cardiac function and improving the efficacy of antichagasic drug treatment of Chagas disease.

### **7.1. Chagas Disease:**

Significance of the problem: The flagellated protozoan *Trypanosoma cruzi* is the etiologic agent of Chagas disease (CD). This parasite is transmitted to humans by insect vectors (*Triatoma infestans*, aka 'vinchuca'), transfusion of infected blood, or from an infected mother to her child, which is currently the main route of transmission in Chile (MINSAL, 2017). It is a disease that affects 7 million people in 21 endemic countries in Latin America and is increasing in non-endemic countries due to migration (WHO, 2015). CD is the second disease with the highest burden among Tropical Diseases (WHO, 2011), with disability-adjusted life years (DALYs) of 806,170. Recent studies estimate that the global economic cost of CD worldwide exceeds USD\$7 billion annually (Requena-Méndez et al., 2017). This figure exceeds that of rotavirus (USD\$ 2 billion) and cervical cancer (USD\$ 4.7 billion) (Lee et al., 2013; Schmunis, 2013). CD causes approximately 8,000 deaths annually, higher than malaria in the Americas (WHO, 2018). The primary CD control strategy includes vector control, systematic screening of blood donors in all endemic countries, detecting and treating congenital transmission, and treating infected children and acute cases (WHO, 2015). However, control programs are discontinuous and current therapy is limited due to low efficacy (WHO, 2015). This is the WHO goal of eradicating or controlling CD by 2020 was far from being achieved (Lenk et al., 2018).

#### **7.1.1. Clinical aspects of the acute and chronic phases of CD:**

Clinically, CD presents an acute phase, diagnosed in less than 10% of cases, due to the absence or presence of mild symptoms. The clinical course, in most cases, is towards spontaneous recovery (Berna, 2015), but without the elimination of parasites. The chronic phase may be asymptomatic (indeterminate), characterized by positive serology and some degree of cardiac involvement evidenced by minimal but persistent inflammation. However, after 10 to 30 years, in about 30% of patients, it progresses to symptomatic forms of the disease, with involvement of the esophagus, colon, or heart (Rassi et al., 2010). Physical symptoms and signs of chronic chagasic cardiomyopathy (CCC) arise from heart failure, cardiac arrhythmias (such as ventricular arrhythmias, atrioventricular block, supraventricular tachycardia, or atrial fibrillation) (Jefferies and Towbin, 2010) and arterial or venous thromboembolism (Rassi et al., 2017a).

#### **7.1.2. Diagnosis:**

The clinical diagnosis of CD in the acute phase is difficult as most infected persons have no symptoms. However, detecting the parasite in the patient's blood is possible by identifying trypomastigotes in the leukocyte coat or by conventional polymerase chain reaction (PCR). In the chronic phase, diagnosis is based on clinical and epidemiological data and serological tests such as a high-sensitivity IgG ELISA and IgG indirect immunofluorescence (Jercic and Oyarce, 2019; MINSAL, 2017). If gastrointestinal involvement is suspected, abdominal radiological studies should be

performed. Cardiac evaluation is essential when making the diagnosis to provide a functional classification and stratify a 10-year mortality risk (Nunes et al., 2018; Rassi et al., 2006; Rassi, 2010). The functional classification helps to explain the evolution of CD. It is based on clinical criteria, NYHA functional classification, chest X-ray, electrocardiogram (ECG), echocardiogram, Holter, thromboembolism, and sudden death criteria and describes stages I to IV (Rassi, 2010). The ECG is useful to detect conduction disturbances, such as atrioventricular or right bundle branch block, which may appear before symptoms manifest (Rojas et al., 2018). A 24-hour Holter should be performed in case of arrhythmias. A chest X-ray is helpful to determine the cardiothoracic index indicative of cardiomegaly. At least an echocardiographic evaluation is also recommended, especially when the ECG is abnormal (MINSAL, 2017).

Different biomarkers have been proposed to assess progression, prognosis, or response to treatment; however, none have demonstrated sufficient specificity to be incorporated as the gold standard for diagnosing Chagas disease (Cortes-Serra et al., 2020). However, brain natriuretic peptide (BNP) and cardiac troponin T (cTnT) have been proposed as useful biomarkers to predict the progression of left ventricular dysfunction (Echeverría et al., 2020). On the other hand, parasite DNA detection is a valuable marker only to determine treatment failure, as a negative result does not exclude parasite persistence (Alonso-Padilla et al., 2017; Parrado et al., 2019).

#### **7.1.3. Chagas Disease is an inflammatory disease:**

The main pathogenic mechanisms explaining CCC are i) parasite-dependent immune-mediated myocardial damage, which is the most critical determinant of the disease (Rassi et al., 2017b), where the TH1/TH2/TReg response is a crucial feature (Acevedo et al., 2018); ii) microvascular abnormalities and ischemia (Borges et al., 2018); and iii) cardiac dysautonomia secondary to autoreactive immune mechanisms (Booney et al., 2019).

